The secondary objective is to study the effect on vascular function, measured with pulse wave velocity (PWV) and inflammatory markers including, CRP, TNFr- 1 and 2, MCP-1, IL-2sR-alfa, IL-6, IL-17, IFN-gamma, Calprotectin, Hyaluronan (HA), compliance and AE.

- **Endpoints**
- **Primary Endpoint**

The primary endpoint is to evaluate the effect of treatment on the blood lipids; Total Cholesterol (TC), Triglycerides (TG), Low density lipoprotein (LDL), High density lipoprotein (HDL) and apolipoproteins in patients with RA and SLE.

- **Secondary endpoints**
- Pulse wave velocity analyses after HCQ-medication
- Blood pressure
- Blood-glucose- and HbA1c levels after HCQ-medication
- Calprotectin levels in serum after HCQ-medication
- Hyaluronan size – and concentration in serum after HCQ-medication
- CRP
- TNFr- 1 and 2, MCP-1, IL-2sR-alfa, IL-6, IL-17, IFN-gamma
- Compliance to treatment
- Adverse events
- Compliance to drug prescription
- **Study Design**
- **Description of Study Design**

This is a randomized, controlled, open label, multi center, interventional study. We will evaluate the effects of HCQ-medication on cardiovaskular risk factors and inflammatory markers in RA and SLE.

- **Justification of Study Design**

**Risk-benefit for the individuals**:

Hydroxychloroquine is approved for treatment of the diagnosis SLE and RA to prevent flare and to lower disease activity, which is the main reason for the prescription of the medication. Hydroxychloroquine has been approved for clinical use for decades and its safety profile is well-documented.

The most common side effects of hydroxychloroquine are nausea and diarrhea, which often improve with time or by taking the medication with food. Less common side effects include skin rashes, changes in skin pigment (such as darkening or dark spots) or hair changes (bleaching or thinning of hair), sensory-motoric disorder, anorexia, tinnitus, dizziness and weakness.

In rare cases, hydroxychloroquine has caused visual changes or loss of vision, but such vision problems are more likely to occur in individuals taking high doses for many years, in elderly patients, or in those with significant kidney disease.
Also neurological hearing disorders (after long-term treatment) and liver defects have been reported in rare cases.

With unknown reporting frequency adverse reactions such as anemia, hypoglycaemia, hearing impairment, psychosis and cardiomyopathy have been reported.

For complete safety information on hydroxychloroquine please see Attachement 2. Summary of Product Characteristics of Plaquenil (Swedish).

The patients in highest risk for developing severe adverse reactions are excluded from the study (see sections 10.2 “Eligibility Criteria” and 14.3 “Concomitant medication and non-drug therapies”). The adverse events and reactions occurring during the study are closely monitored (see sections 12. “Withdrawal Criteria and Early Termination” and 15. Adverse Event and Serious Adverse Event Collection, Recording and reporting”) and the actions will be taken to treat the reactions and mitigate the risk for worsening. The short period of drug treatment (8 weeks) will decrease the likeliness of developing long-term treatment adverse reactions.

To receive information in writing about the increased risk of CVD can worry the patient. However, we do have a strategy in answering the patients´ questions and also a structured plan for dealing with cardiovascular risk factors that need direct medical intervention. The patients will be able to reach the study nurse by phone at every site and if needed, the investigator is available for answers. If risk factors for CVD are in need of direct investigation or medical treatment, the patient will be remitted for this as in clinical praxis.

Taking part of the study will take a sufficient amount of time for the patient. However, the study is optional and contains a rigorous amount of tests regarding cardiovascular risk factors, which is of potential benefit for the patients.

Twenty patients in each group are needed for a 80%-ig power of lowering blood-pressure 10 mmHg. Lowering LDL or TC 0.65 mmol/L with SD 0.7 gives a power of 0.816 when 20 patients in each group are included.

- **Stop Criteria for the Study**

If any new alarming information regarding the safety profile of hydroxychloroquine in the studied population comes to the spnsoror´s knowledge during the trial, immediate actions will be taken to assess whether the study is to be stopped. See also section 17.5 “Study Closure”.

- **Study Visits**

Patients with RA and SLE will be recruited from the Rheumatology departments in Umeå, Sundsvall, Sunderbyn and Östersund. Our intention, if possible, is to recruit the same amount (n=24) of patients from each diagnoses. Patients full filling the classification criteria for RA (ICD-10 M05.9) and SLE (ICD-10 M32.9) and without ongoing HCQ-medication, will be invited to participate in the study. Information about the study, with informed consent and return envelope, will be sent by post, to the patients. The patient information will include name and phone number to nurse and physician from each center, for patients to ask any questions about the study. If the patient agrees to participate, a screening visit is booked with-in 2-3 weeks.

Two-three weeks before week 0 a **screening** visit is performed. After screening, randomization is performed.

Group 1 starts HCQ-medication at week 0. **Assessments** are performed at week 0, 4 and 8. After this the patients may continue the study medication outside the study due to the diagnose RA or SLE.

Group 2 starts HCQ-medication at week 4. **Assessments** are performed at week 0, 4, 8 and 12. After this the patients may continue the study medication outside the study due to the diagnos RA or SLE.

See attachment 1. Schedule of events for more detailed description of the study procedures.

Each visit for assessments with blood samples and measurements of PWV takes 30 minutes + 30 min.

The medical treatment period within the study is 8 weeks for both groups. But the medication may continue due to the disease and diagnose.

**Screening:** Informed consent, inclusion and exclusion criteria are controlled (10.2). Disease activity is investigated regarding the diagnosis, **SLEDAI-2k** (attachment 3) for SLE and **DAS-28** (attachment 4) for RA. Medical history and present medication is recorded. Vital signs are investigated. For pre-menopausal women a pregnancy test is performed. Blood samples for analyses regarding disease activity is included in each diagnose-specific index (SLEDIA-2k and DAS 28). Analyses regarding blood lipids will also be performed (see also schedule of events). The screening visit takes 1.5 hour. After screening visit the patients are coded and randomly assigned to group 1 or group 2.

**SLEDAI-2k** is a disease activity index in SLE calculated from count of activity in all organs involved in this disease: Neuropsychiatric signs, visual disturbance, lupus headache, cerebrovascular incidence, vasculitis, arthritis, myositis, skin manifestations, serositis, signs of nephritis, hematological or serological manifestations and fever are recorded in this index (34).

**DAS-28** is a disease activity index in RA, used in every day-clinic. It is calculated from investigation of 28 joints, according to “swollen joints” and “tender joints”. Knees, shoulders, elbows, wrists, metacarpo-phalangial and proximal interphalangial joints are included in DAS-28. Patients global health, sedimentation rate, C-reactive protein-level and Health Assessment Questionnaire are also included in the calculation of DAS-28 (35).

Patients with RA (n=24) and SLE (n=24) will be recruited from the Rheumatology depart-ments in Umeå, Sundsvall, Sunderbyn and Östersund. 12 patients with RA and 12 patients with SLE will be randomized to each group. The randomization will be performed by study nurses, not otherwise involved in the conduction of the study, so that patients with RA receive even study numbers (Group 1 or Group 2) and patients with SLE (Group 1 and Group 2) receive uneven study numbers. A randomization list definining each study numbers group identity/treatment regim is prepared in advance by the study team.

- **Eligibility Criteria**
- **Inclusion Criteria**
- Male and female, 18-65 years that have given their written consent to participate in the study; Women of Childbearing Capacity (WOCBC) only if willing to comply with effective contraception methods during the course of trial . Acceptable methods are such as oral contraceptives, contraceptive patches, contraceptive implant, vaginal contraceptive, double-barrier methods (for example, condom and spermicide), intrauterine device (IUD), hormonal IUD.
- ACR criteria for RA and SLE (4)
- < 10mg Prednisolon daily doses
- Low-medium disease activity = DAS28 <4.6-RA, SLEDAI <6 SLE (Arthritis accepted)
- **Exclusion Criteria**

A subject will not be eligible for inclusion in this study if any of the following criteria applies:

- Antimalarial medication less than 5 ½-t i.e. 250 days before inclusion visit
- High disease activity, where cortison adjustment is predictable
- Pleuritis or Pericarditis – SLE
- Impaired visus and/or color vision
- Auditory nerve damage
- Cardiomyopathy
- Brach block / atrioventricular block
- Hypertension >160/95
- Diabetes
- Ongoing medical treatment with digoxin
- Re-introduction or recent (within 2 weeks) change in the dosing of NSAIDs, prednisolon, blood pressure lowering medication or antilipide treatment and within 6 weeks for disease-modifying agents
- Serious comorbidity, including other medications with known drug interactions with medication intended in the present study
- Short life expectancy due to other comorbidity
- Documented allergy or intolerance to the study drug.
- Severe psychiatric condition or other reason that jeopardize compliance with visit schedule
- In case of women of child bearing capacity (WOCBC), pregnancy assessed by anamnesis and pregnancy test
- **Other Eligibility Criteria Considerations**

To assess any potential impact on subject eligibility with regard to safety, the investigator must refer to the following documents for detailed information regarding warnings, precautions, contraindications, adverse events (AEs) and other significant data pertaining to study drug: Approved national summary of product characteristics (SPC).

- **Treatment within the study**

Hydroxychloroquine (Plaquenil®) 200 mg (Attachment 2. Summary of Product Characteristics) one tablet daily is initiated week 0 for group 1 and at week 5 for group 2and will be continued after the study is closed. All other medication continues during study, but if changes is performed in any medication, that might be a reason for discontinuation in the study (se also Section12.).

- **Withdrawal Criteria and Early Termination**

The subjects have the right to withdraw from the study at any time and for any reason without prejudice to his or her future medical care by the physician or hospital. The investigator also has the right to withdraw subjects from the study in the event of change in eligibility or other reasons.

Discontinuation criteria for individual subjects:

- Withdrawal of consent
- Changes in glucocorticoids, NSAID, ASA as well as medication against hyperlipidemia and hypertension
- Adverse event or serious adverse event related to treatment or investigational procedure that requires discontinuation in the study according to the investigator
- Pregnancy during the study
- **Study Assessments**
- **Demographic and Baseline Assessments**

Demographic information such as gender, age and ethnic origin will be collected in addition to baseline values.

Other baseline assessments are:

- Signed and dated ICF
- Inclusion/exclusion criteria
- Disease history/duration
- Current medication
- Disease activity by index (SLEDAI-2k or DAS 28)
- Vital signs
- WOCBC, pregnancy test
- Visus and color vision
- Blood lipids and-glucos
- See also Schedule of events, Attachment 1.
- **Assessments during the study**

Assessments include blood lipids, vascular stiffness, Calprotectin and Hyaluronan as described in 7.1 and 7.2 and 9.1.
In addition;

- Compliance to treatment
- Adverse events
- Compliance to drug prescription
- **Biobank**

Biobank is available at the Rheumatology Clinic, NUS, Umeå, Sweden (SoS443)

- **Study medication and concomitant medication/therapy**
- **Study medication per treatment group**

Hydroxychloroquine (Plaquenil®) 200 mg one tablet daily. See also risk-benefit for the individuals (4.2).

- **Administration follow-up of the medication:**

The responsible physicians for the patients will prescribe the study medication to the patients. In case of an adverse event, the study personnel will contact the sponsor. The sponsor will determine whether the event qualifies to immediate reporting to the regulatory authorities (SUSARs) or will be included to the annual development safety update report to Regulatory Authority (SAE). SAEs occurring after trial termination must be reported if considered related to the treatment during the trial.

- **Concomitant Medications**

The prohibited medication are considered at the time of inclusion (see section 10.2.2 “Exclusion Criteria”) and prevent the inclusion of patient not compliant to inclusion/exclusion criteria due to such ongoing medication.

During the study, all concomitant medications taken in both groups studied will be recorded in the patient record according to standard practice. In case a prohibited medication is noticed it results to patient withdrawal from the study (see sections 11. “Treatment within the Study” and 12. “Withdrawal Criteria and Early Termination”).

- **Adverse Event and Serious Adverse Event Collection, Recording and Reporting**

Known complications of RA and SLE will not be considered as a AE/SAE.

The investigator is responsible for detection and documentation of events meeting the criteria and definition of an adverse event (AE) or serious adverse event (SAE), as provided in this protocol. During the trial when there is a safety evaluation, the investigator or site staff will be responsible for reporting AEs and SAEs, as detailed in this section of the protocol. Clinically significant AEs considered by the investigator to be related to treatment will be followed until resolved or considered stable. It will be left to the investigator’s clinical judgment to determine whether an AE is related and of sufficient severity to require the subject’s removal from treatment or from the trial. A subject may also voluntarily withdraw from treatment due to what he or she perceives as an intolerable AE. If either of these situations arises, the subject should be strongly encouraged to undergo an end of trial assessment and be under medical supervision until symptoms cease or the condition becomes stable.

- **Definition of Adverse Events and Serious Adverse Events**
- **Definition of an Adverse Event**

An AE is defined as any untoward medical occurrence in a clinical trial subject administered a medicinal product and which does not necessarily have a causal relationship with this treatment. An AE can therefore be any unfavorable and unintended sign (including an abnormal laboratory finding), symptom, or disease (new or exacerbated) temporally associated with the use of a medicinal product, whether or not considered related to the product. For marketed medicinal products, this also includes failure to produce expected benefits (i.e. lack of efficacy), abuse or misuse.

- **Definition of a Serious Adverse Event**

A SAE is defined as any untoward medical occurrence or effect, that at any dose:

- Results in death
- Is life threatening
- Requires hospitalization or prolongation of existing hospitalization
- Results in persistent or significant disability or incapacity
- Is a congenital anomaly or a birth defect
- Is an other significant medical hazard

An AE necessitating hospitalization meets the regulatory definition for “serious” if the inpatient hospital admission includes a minimum of an overnight stay in a health care facility. Any AE that does not meet one of the definitions of serious (e.g. an AE requiring an emergency room visit, outpatient surgery or requires urgent investigation) may be considered by the investigator to meet the “other significant medical hazard” criterion for classification as a SAE. Examples include allergic bronchospasm, convulsions and blood dyscrasias.

- **Definition of a Suspected Unexpected Serious Adverse Reaction**

A SUSAR is both unexpected (not consistent with the applicable product safety reference information) and also meets the definition of a Serious Adverse Event/Reaction. The causal relationship with the treatment is defined as possible by the investigator.

For the purpose of this trial, the reference safety information defining what is to be considered as SUSAR is the Summary of Product Characteristics of Plaquenil (attachment 2).

- **Disease-Related Events and/or Disease-Related Outcomes Not Qualifying as AEs/SAEs**

Expected signs of disease activity such as joint stiffness and joint pain in RA and SLE or exantema in SLE that are well defined as disease related and do not qualify as AEs/SAEs.

- **Clinical Laboratory Abnormalities and Other Abnormal Assessments as AEs and SAEs**

Abnormal laboratory findings (e.g. clinical chemistry, hematology and urinalysis) or other abnormal assessments that are judged by the investigator as clinically significant will be recorded as AEs or SAEs if they meet the definition of an AE or SAE. Clinically significant abnormal laboratory findings or other abnormal assessments that are detected during the trial or are present at baseline and significantly worsen following the start of the trial will be reported as AEs or SAEs. However, clinically significant abnormal laboratory findings or other abnormal assessments that are associated with the disease being studied, unless judged by the investigator as more severe than expected for the subject’s condition, or that are present or detected at the start of the trial and do not worsen, will not be reported as AEs or SAEs.

The investigator will exercise his or her medical and scientific judgment in deciding whether an abnormal laboratory finding or other abnormal assessment is clinically significant.

- **Reporting of Adverse Events**

The investigator is responsible for ensuring that all AEs (as defined in Section 11.1) observed by the investigator or reported by subjects are properly captured in the subjects’ medical record. In addition, the investigator is responsible for ensuring that all AEs captured on the subjects’ medical records are reported on the CRF. If a subject is permanently withdrawn from the trial because of an SAE, this information must be included in the initial or follow-up SAE report form, as well as the End-of-Trial form. In case of withdrawal due to an AE, then the AE report form and as well as the End of Trial form will be completed. AEs either reported by the patient or observed by the investigator should be described in the following manner:

- The nature of the event will be described in precise, standard medical terminology (i.e. not necessarily the exact words used by the patient). If known, a specific diagnosis should be stated.
- The intensity of the AE will be described in terms of **mild, moderate or severe** according to the investigator’s clinical judgment. The intensity must be independent of the assessment of the seriousness of the AE.

**Mild:** Transient symptoms, no interference with the subject’s daily activities, acceptable.

**Moderate:** Marked symptoms, moderate interference with the subject’s daily activities but still acceptable.

**Severe:** Considerable interference with the subject’s daily activities, unacceptable.

The duration of the event will be described by the start date and end date.

**Related**: Related AEs or SAEs are classified as adverse reaction (AR) or serious adverse reaction (SAR).

**Probable**: Good reason and sufficient documentation to assume a causal relationship between prescribed medication and the AE. Probable related AEs or SAEs are classified as adverse reaction AR or SAR.

**Possible**: A causal relationship is likely and cannot be excluded. Possible related AEs or SAEs are classified as AR or SAR.

**Unlikely**: The event is most likely related to etiology other than any of the study drugs.

**Unknown**: Impossible to assess e.g. because of insufficient evidence, conflicting data or poor documentation.

**Not related**: No relationship to any of the study drugs.

The outcome of the event will be described in terms of:

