| Safety evaluation  Safety evaluation | For safety evaluation, the subjects are monitored for compliance including adverse events occurrence. The compliance is measured by controlling drug accountability during patients´site visits. From the time a patient consents to participate in the trial until he/she has completed the trial (without any follow up period), all AEs will be reported in the CRF. All SAEs as defined in the protocol will be reported by filling out and sending the SAE form within 24 hours to *the monitor*. *The sponsor* will determine whether the event qualifies to immediate reporting to the regulatory authorities (SUSAR-reporting) or will be reported in the annual development safety update report (DSUR). SAEs occurring after trial termination must be reported if considered related to the treatment during the trial. |
| Statistical methods | Non-parametric tests will be used. Mann-Whitney´s test; when comparison between groups. Statistical testing of multiple assessments over time; Kruskal-Wallis or Friedmans test and Wilcoxons test. |
| Criteria for evaluation | All subjects enrolled will constitute the analysis population  Primary and secondary endpoints (except safety parameters) will be analyzed according to intention to treat.  Safety parameters will be analyzed as per protocol. |
| Interim analysis | No interim analysis is planned |

- **Background and Rationale**
- **Background**

The two inflammatory diseases Rheumatoid Arthritis (RA) and Systemic Lupus Erythemato-sus (SLE) have the major comorbidity problem of Cardiovascular diseases (CVD) in common. The risk for CVD is overall more than doubled in both RA (1) and SLE compared with population/controls. In SLE, this risk for CVD is emphasized and noted 8 times increased in middle aged women (2, 3). In our further studies of surrogate markers and risk factors for CVD, we could show both an increased Intima-Media thickness and decreased endothelial function in RA compared with controls (4, 5). In SLE we have shown an increased vascular stiffness compared with controls (6). Traditional risk factors (e.g. dyslipidemia and hypertension) for CVD are increased in RA and SLE although with diverging results (7-10).

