Subjects who become pregnant during the trial must be withdrawn. The subject will be asked to attend follow-up visits and the outcome of the pregnancy will be followed including reporting on the state of the child 8 to 12 weeks after delivery. Patients receiving treatment shall not breast feed their children.

- **Data Analysis and Statistical Considerations**
- **Sample Size Considerations**

Twenty patients in each group are needed for a 80%-ig power of lowering blood-pressure 10 mmHg. Lowering LDL or TC 0.65 mmol/L with SD 0.7 gives a power of 0.816 when 20 pati-ents in each group are included.

- **Data Sets and Populations**

All subjects enrolled will constitute the analysis population.

- **Interim Analysis**

No interim analysis will be performed

- **Key Elements of Analysis Plan**

Non-parametric tests will be used. Mann-Whitney´s test; when comparison between groups. Statistical testing of multiple assessments over time; Kruskal-Wallis or Friedmans test and Wilcoxons test.

- **Study Administration**
- **Procedure for obtaining informed consent**

Eligible individuals in the study will be contacted by mail containing information about the study, informed consent and return envelope.

- **Definition of Source Data**

All completed assessment scales will be collected in patient specific binders and regarded as source data. All patient related activities of medical relevance will also be documented in the patient hospital record

- **Quality Control**

The trial will be monitored consistent with the demands of the trial and site activity to verify that the:

- Safety and rights of subjects are being protected
- Data are authentic, accurate, and complete
- Trial is conducted in accordance with the currently approved protocol and any other trial agreements, GCP and all applicable regulatory requirements. The investigator and the head of the medical institution (where applicable) agrees to allow *the monitor* direct access to all relevant documents.

An external monitor for the study, not involved in any aspect of the treatment of the individuals participating in the study, will be appointed. The monitor will be appropriately trained, and has the scientific and/or clinical knowledge needed to monitor the trial adequately.

The monitoring will take place in accordance to GCP before, during and after the trial. If any misconduct or neglect would be notified the sponsor and investigator will be notified for to corrective and preventive actions.

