ATTACHMENT 1. SCHEDULE OF EVENTS

| **Procedures** | **Screening**  **Week -2;** for eligible patients thereafter **Randomization** | **Week 0** | **Week 4** | **Week 8** | **Week 12 #** |
| --- | --- | --- | --- | --- | --- |
| Informed consent | X |  |  |  |  |
| Inclusion/Exclusion  Criteria | X |  |  |  |  |
| SLEDAI-2k (SLE) | X |  |  |  |  |
| DAS 28 (RA) | X |  |  |  |  |
| Medical history and present medication | X | X |  |  |  |
| Vital signs (pulse and blood pressure) | X |  |  |  |  |
| Pregnancy test* | X |  |  |  |  |
| Visus Color vision | X |  |  |  |  |
| Blood samples: |  |  |  |  |  |
| Chol | X | X | X | X | X |
| TG | X | X | X | X | X |
| HDL | X | X | X | X | X |
| LDL | X | X | X | X | X |
| ApoA1 |  | X | X | X | X |
| ApoB |  | X | X | X | X |
| Lp(a) |  | X | X | X | X |
| HbA1c | X | X | X | X | X |
| B-glc | X | X | X | X | X |
| CRP |  | X | X | X | X |
| Serum for storage  -20◦C. |  | X | X | X | X |
| PWV including  Pulse and blood  pressure |  | X | X | X | X |
| Adverse events |  |  | X | X | X |
| Compliance to drug prescription |  |  | X | X | X |

* For WOCBC

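### No outcome sampling is provided for after discontinuation for a background-medication change, although intention to treat is promised, and Sections 11, 12 and 14.3 disagree on the rule

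*Protocol*

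**What the plan says.** Three sections of the protocol describe what follows a medication change.

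- **Section 12** (Withdrawal Criteria and Early Termination) gives, as a discontinuation criterion for individual subjects and without qualification: "Changes in glucocorticoids, NSAID, ASA as well as medication against hyperlipidemia and hypertension".
- **Section 14.3** (Concomitant Medications) says: "In case a prohibited medication is noticed it results to patient withdrawal from the study". It refers to Sections 11 and 12.
- **Section 11** (Treatment within the study) is softer: "if changes is performed in any medication, that might be a reason for discontinuation in the study". It also refers to Section 12.

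On the analysis, the Synopsis (Criteria for evaluation) says: "Primary and secondary endpoints (except safety parameters) will be analyzed according to intention to treat". Section 16.1.1 adds: "All subjects enrolled will constitute the analysis population".

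On the outcomes, Section 7.1 says: "The primary endpoint is to evaluate the effect of treatment on the blood lipids". Blood pressure, pulse wave velocity (PWV), CRP and the other inflammatory markers are secondary (Section 7.2). Section 8.2 says of patients in the study: "If risk factors for CVD are in need of direct investigation or medical treatment, the patient will be remitted for this as in clinical praxis".

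**The concern.** Intention to treat needs the outcomes of every randomised patient, whatever happened to their treatment. Section 12 does not separate stopping study drug from leaving the study, and Sections 11 and 14.3 speak of leaving the study. If patients leave when a listed drug is changed, their remaining samples are not taken.

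The listed drugs are also tied to the endpoints. Lipid-lowering and blood-pressure drugs are changed because of lipids and blood pressure. Steroids and NSAIDs are changed because of disease activity, which goes with the inflammatory markers. The trial is open label, so prescribing can depend on the known group. Missing values may therefore be related both to outcome and to group, and a comparison of those who remain may be biased.

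**Working it through.** **1. The plan's power figure.** Inputs from Section 16.1: difference 0.65 mmol/L, SD 0.7, 20 per group. Two-sided alpha of 0.05 is my assumption, as the protocol states none. Standardised difference = 0.65/0.7 = 0.929. Two-sample t-test power = 0.8163, which reproduces the stated 0.816. For the planned Mann-Whitney test with normal data, power at 20 per group is 0.797 by asymptotic relative efficiency (ARE) and 0.791 by simulation.

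Section 10.1 randomises 12 RA and 12 SLE patients to each group, so 24 per group. The margin is 24 − 20 = 4 per group, or 4/24 = 16.7%.

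| Patients left per group | t-test power | Mann-Whitney power (ARE) |
|---|---|---|
| 24 | 0.883 | 0.867 |
| 22 | 0.853 | 0.836 |
| 20 | 0.816 | 0.797 |
| 18 | 0.772 | 0.752 |
| 16 | 0.720 | 0.698 |

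**2. Is anyone measured after discontinuation?** I found no provision for it. The only assessment offered to a patient who leaves is an end-of-trial assessment in the introduction to Section 15. It is encouraged rather than required, and applies to adverse-event cases. That paragraph does distinguish removal from treatment and removal from the trial. Section 12 does not use the distinction.

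**3. Which visits are exposed?** Attachment 1 schedules lipids at screening and at weeks 0, 4, 8 and 12 (week 12 for the control group only), and PWV with blood pressure at weeks 0, 4, 8 and 12.

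- *Change prompted by a week 4 lipid or pressure value.* The week 4 value is already recorded. What is lost is week 8 and, in Group 2, week 12.
- *Change prompted by a week 8 value.* Group 1 has finished. Group 2 loses week 12.
- *Change prompted by a screening or week 0 value.* Randomisation follows screening, so week 4 could be lost. The trigger precedes treatment, so HCQ cannot have influenced it, though the decision to prescribe may be influenced by known allocation.
- *Steroid or NSAID change between weeks 0 and 4.* Week 4 is lost. Section 8.2 says HCQ is used to prevent flare and lower disease activity, so such changes could be commoner in the group not yet treated. It gives no time to effect.

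The week 4 comparison, treated against not yet treated, is therefore exposed mainly by the last route. Weeks 8 and 12, which feed the tests over time, are exposed by the referral route.

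**4. Scale, by assumption only.** If lost and retained patients differ by the same gap in both groups, bias in the contrast = (loss share in Group 2 − loss share in Group 1) × gap. The protocol gives none of these inputs.

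| Assumed loss, Group 2 / Group 1 | Assumed gap (mmol/L) | Bias (mmol/L) | Share of 0.65 |
|---|---|---|---|
| 20% / 10% | 0.5 | 0.10 × 0.5 = 0.05 | 7.7% |
| 20% / 5% | 0.5 | 0.15 × 0.5 = 0.075 | 11.5% |
| 20% / 5% | 1.0 | 0.15 × 1.0 = 0.15 | 23.1% |

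For comparison, the standard error of the difference with 20 per group is 0.7 × √(2/20) = 0.22 mmol/L. If either the gap or the difference in loss has the opposite sign, the bias reverses.

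**The case against.** Much can be said for the plan. Stable co-medication is a recognisable way to isolate a lipid effect. Follow-up is short. Section 10.2 limits disease activity and excludes predictable cortisone adjustment, recent changes in these drugs and hypertension above 160/95, so losses may be few. All enrolled subjects stay in the nominal population, values before discontinuation remain usable, and the handling of missing data can be left to an analysis plan. These points limit the likely size. They do not supply the samples.

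A reader might infer more than the protocol supports:

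- *That every change leads to removal.* Section 11 says *might*, and it is not plain that a dose change in a permitted drug is a prohibited medication under Section 14.3. The sections conflict; they do not set one clear rule.
- *That medication changes go unchecked after week 0.* Attachment 1 marks "Medical history and present medication" only at screening and week 0, but Section 14.3 has all concomitant medication recorded in the patient record during the study.
- *That referral removes the worst lipid values from the week 4 contrast.* No lipid or pressure value is scheduled between weeks 0 and 4, and a value that prompts referral at week 4 has already been collected.
- *That a bias of known size follows.* The illustration joins a loss difference, for which flare is the likelier reason, to a lipid gap, for which referral is. No text puts both in the same patients.
- *That the power margin would be exhausted.* Losses of 20% and 5% leave about 19.2 and 22.8 patients, equivalent to 2 × 19.2 × 22.8/42 = 20.8 per group, with t-test power of about 0.83.

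**Conclusion.** The point holds in a limited form. Sections 11, 12 and 14.3 do not agree on whether a medication change ends participation. The protocol provides no outcome measurement after such a discontinuation, while promising intention to treat for all enrolled subjects. This is a matter of data collection, so the absence of an analysis plan does not excuse it.

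The missing values may be related to outcome and to group, mainly at weeks 8 and 12 and possibly at week 4. The size and direction of any bias are unknown. The figures of 0.05 to 0.15 mmol/L rest wholly on assumed loss rates and gaps and are not an estimate for this trial. The loss of power is secondary: up to four losses per group still leave the 20 in the power statement. To say that intention to treat is impossible would go too far. It would be incomplete for these patients, to an extent that the protocol leaves open. The change is worth making because it is cheap and serves the protocol's own analysis principle.

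**What to change.** 1. Reconcile Sections 11, 12 and 14.3, so that they say the same about what a medication change leads to, and distinguish stopping study drug from leaving the study.
2. State that, after a change in a listed medication, the patient stays on the visit schedule and the remaining scheduled lipid, blood-pressure, PWV and inflammatory-marker measurements are taken unless consent is withdrawn.
3. Analyse all randomised patients as allocated, with a sensitivity analysis that excludes values taken after the change.
4. Optionally, mark present medication at weeks 4, 8 and 12 in Attachment 1, so that the recording stated in Section 14.3 is tied to visits and the date of a change is known.

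The cost is a short amendment, one CRF line per visit and slightly more data collection. The drawback is that some values will be taken under changed background therapy, which the sensitivity analysis addresses. The proposal concerns outcome measurement only and takes no view on who should continue, change or stop any treatment.
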